### Interventions

The IG will receive LLLT using an Inbramed® system, which emits laser light in the red spectrum (wavelength 660 nm and power 30 mW). The application will occur over the center of the injured area in sweep mode, with the laser tip at least 1 cm away from the bleeding area. At the wound edges and at a distance from the lesion, application will be performed in spot mode, with the laser tip leaning against the skin. The laser tip will be covered with a clear, disposable polyvinyl chloride lens to prevent infection and contamination as a result of direct contact with the lesion. The nurse and patient will wear personal protective eyewear rated for laser use. After laser therapy, a conventional dressing will be applied, and self-care guidelines will be given to the patient as clinically indicated.

The CG will receive conventional treatment alone, which constitutes conventional wound dressing and application of topical medication as indicated by the characteristics of the ulcer and perilesional area (including silver or calcium alginate, petrolatum-impregnated gauze, medium-chain triglycerides, papain, hydrogel, or solid petroleum jelly), followed by compressive therapy and patient self-care guidance as clinically indicated.

### Study protocol

Patients eligible for the study will be divided into two groups (IG and CG) (Fig. 2). IG patients will receive LLLT as an adjunct to conventional treatment. CG patients will receive conventional treatment alone. After the interventions, patients from both groups will receive guidance on self-care at home.

**Fig. 2 Fig2:**
[figure not shown]
Flow chart of study participation and interventions.ICF, informed consent form, NOC Nursing Outcomes Classification, RCT randomized controlled trial

Conventional treatment in CG participants will be provided by a staff nurse in the outpatient wound-care clinic who has clinical experience in the care of patients with venous ulcers. IG participants will be treated by a nurse who has similar clinical experience in wound care and is also a trained laser therapist. All nurses have been trained in the standard procedures for venous ulcer care and the clinical indicators of NOC outcomes to evaluate these lesions.

In both groups, an evaluation of healing will be carried out by assessing the 14 constituent clinical indicators of the NOC outcomes for wound healing (secondary intention; 1103) and tissue integrity (skin and mucous membranes; 1101). The 14 clinical indicators are foul wound odor, macerated skin, surrounding skin erythema, edema, granulation, decreased wound size, scar formation, pain, pruritus, abnormal pigmentation, thickness, necrosis, hydration/skin scaling, and exudate. Each clinical indicator will be evaluated using a 5-point Likert scale, where the lowest score denotes the worst possible outcome, and the highest score, the best possible outcome.

In both groups, patients will be monitored weekly until complete repair of the ulcer or for a maximum of 16 weeks. The frequency of LLLT application for this protocol was based on previous studies of phototherapy for chronic wounds [12–16]. The duration of treatment was determined based on the average healing period of a chronic wound [7–12].

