## Abstract

**Background:**

Different methods are available for the treatment of venous ulcers. Most current approaches focus on a combination of topical and compressive therapy. Adjuvant low-level laser therapy may be helpful in lesions with a protracted healing course, but evidence for its use is still limited. This paper describes the protocol of a randomized controlled trial designed to compare the effect of adjuvant low-level laser therapy versus conventional venous ulcer tissue repair, evaluated by a nurse using clinical indicators from the Nursing Outcomes Classification (NOC).

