### Evaluation of tissue regeneration

The monitoring of tissue regeneration is based on a nurse’s clinical judgment regarding the characteristics of the wound in relation to its bed, its edges, and the perilesional skin. This evaluation guides the choice of wound-care medication to be used, but is susceptible to evaluator error, because there are no standardized clinical indicators.

The evaluation of tissue regeneration can be enhanced using classification systems. Among such systems, the Nursing Outcomes Classification (NOC) is particularly interesting as it provides a list of clinical indicators for evaluating a patient’s condition and the clinical course. These indicators are scored on 5-point Likert scales (range 1 to 5), in which the lowest score represents the worst possible state and the highest score represents the most desirable state after implementation of interventions [9–17]. However, research into the clinical applicability of the NOC in wound evaluation is still incipient, which makes it impossible for nurses to know which clinical indicators to measure during the clinical follow-up of patients with venous ulcers. This randomized clinical trial should provide clinical evidence of the effect of LLLT as an adjuvant treatment for venous ulcers when compared to conventional topical treatment. Intervention effects and clinical evolution will be assessed through a reliable, validated method, namely, the clinical indicators of the NOC.

The aim of this article is to describe the protocol of a randomized controlled trial designed to compare the effect of conventional venous ulcer treatment with adjunctive LLLT versus conventional treatment alone. Throughout, patients will be evaluated with the clinical indicators described in the NOC.

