### Outcomes

#### Primary outcome

The primary outcome is decreased wound size and scar formation based on NOC outcome wound healing (secondary intention; 1103).Wound area in cm^2^ (measured as the product of the longest dimension in the cephalocaudal direction by the widest dimension), evaluated by a Likert scale, with 1 being the worst possible score and 5 the best possible score. Each Likert scale score of the Decreased wound size indicator has an operational definition that corresponds to the size in cm^2^.Wound covered with epithelial tissue (new pink or bright tissue that develops from the wound edges or as islands on the surface of the wound), evaluated by a Likert scale, with 1 being the worst possible score and 5 the best possible score.

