### Independent/exposure and confounding variables

The main exposure variable will be the tissue repair process in the CG and IG. The impact of each management strategy on the outcomes will be controlled by monitoring the following confounding variables: pharmacotherapy or co-intervention at another health facility or by another professional.

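### Each arm is treated by a different nurse, so nurse care, and possibly nurse scoring, is confounded with the laser effect

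*Protocol article*

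**What the plan says.** The Study protocol section (text after the Fig. 2 legend) fixes who treats whom. For the control group: "Conventional treatment in CG participants will be provided by a staff nurse in the outpatient wound-care clinic". For the laser group: "IG participants will be treated by a nurse who has similar clinical experience in wound care and is also a trained laser therapist". Nothing in the article has a nurse work in both arms.

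The treating nurse has discretion. Under Interventions, conventional care includes "application of topical medication as indicated by the characteristics of the ulcer and perilesional area", with several products listed, and self-care guidance is also given as the clinical picture requires.

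On scoring, the same section says "All nurses have been trained in the standard procedures for venous ulcer care and the clinical indicators of NOC outcomes to evaluate these lesions". It does not say which nurse records the scores. The Abstract refers to evaluation by a nurse, with no mention of independence or masking. No sham laser is described, and under Randomization the patient opens the allocation envelope.

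The confounders to be monitored are "pharmacotherapy or co-intervention at another health facility or by another professional". The trial's own treating nurses and scorers are not among them, and Statistical analyses contains no nurse term.

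**The concern.** A randomized comparison attributes a difference between arms to the treatment because everything else is balanced by chance. Here the nurse is not balanced: she is assigned with the arm. Two routes to bias follow, and they rest on different evidence.

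- **Care.** If one nurse chooses dressings more aptly, teaches self-care better or spends more time with patients, the wounds in her arm heal differently with no laser effect at all. This route follows directly from the stated staffing.
- **Scoring.** If each treating nurse also scores her own patients, a difference in leniency, or an expectation about the laser in a nurse who has just applied it, enters the outcome. This route is conditional, because the scorer is not named.

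At stake is whether a positive result can be credited to the laser. Recruiting more patients does not help: it narrows the interval around the laser effect and the nurse effect added together.

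**Working it through.** **Inputs from the article.** Sample size: a 1-point difference on an NOC indicator, 80% power, 5% significance, 17 per group, 20 per group recruited. Statistical analyses: two-tailed test, Student's t-test between groups.

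**Assumed inputs.** The score SD is taken from a cited source and not printed; SD = 1 is assumed. The number of nurses per arm is not given; one and three are shown. The between-nurse SD (s = 0.2 to 0.3 points) and the fixed shifts (0.25, 0.5 and 1 point) are illustrations.

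**Step 1: does SD = 1 fit the plan's own figure?** The noncentral-t calculation for a 1-point difference gives 17 per group (power 0.807; 16 per group gives 0.781). This matches the stated 17. An SD of 0.9 would need 14 per group and 1.2 would need 24. So SD = 1 is consistent with the plan, though not confirmed by it.

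**Step 2: what can be estimated.** With one nurse per arm there are 2 nurses and 2 arms, which leaves 2 − 2 = 0 degrees of freedom for nurses. With several nurses per arm and no overlap, nurse variation within an arm can be seen, but the two sets of nurses still differ by arm.

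**Step 3: nurse effect as random variation, no laser effect, n = 20 per arm, k nurses per arm.**

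Variance of the difference in means = 2/20 + 2s²/k. The planned test assumes only 2/20 = 0.1, a standard error of 0.316, and rejects beyond 2.02 × 0.316 = 0.64. Type I error = 2 × [1 − Φ(0.64/√variance)].

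| k | s | variance | SE | type I error |
|---|---|---|---|---|
| 1 | 0.2 | 0.1 + 0.08 = 0.18 | 0.424 | 13% |
| 1 | 0.25 | 0.1 + 0.125 = 0.225 | 0.474 | 18% |
| 1 | 0.3 | 0.1 + 0.18 = 0.28 | 0.529 | 23% |
| 3 | 0.2 | 0.1 + 0.027 = 0.127 | 0.356 | 7% |
| 3 | 0.3 | 0.1 + 0.06 = 0.16 | 0.400 | 11% |

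These use the normal distribution with the t cut-off. Replacing it with t on 38 degrees of freedom raises each figure by about one percentage point.

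**Step 4: nurse effect as a fixed shift b, no laser effect.** Noncentrality = b/√(2/n). For b = 0.5 and n = 20 this is 0.5/0.316 = 1.58.

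| shift b | 17 per arm | 20 per arm |
|---|---|---|
| 0.25 | 11% | 12% |
| 0.5 | 29% | 34% |
| 1 | 81% | 87% |

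A half-point shift is half of the 1-point effect that the trial is sized to detect.

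**The case against.** The strongest reply concerns scoring. A reader might infer that an unmasked laser therapist scores her own patients. The text does not say so. It says the nurses were trained in the indicators, and the Abstract's single nurse would equally fit one assessor for both arms. The article is condensed, and its figures and checklist are not shown. That objection stands, so the scoring part is put only as a condition.

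A reader might also take the Background remark that nurse judgment "is susceptible to evaluator error, because there are no standardized clinical indicators" as an admission about this trial. It is not: the sentence describes judgment without standard indicators, and the protocol offers the NOC as the remedy.

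Nor are all the indicators equally subjective. For wound size, "Each Likert scale score of the Decreased wound size indicator has an operational definition that corresponds to the size in cm^2", so leniency has less room there than for scar formation or pain. This protects the scoring only. A real difference in dressing or teaching would change the wound area itself.

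Similar experience and common training are stated safeguards. They may shrink the nurse difference; they do not make it estimable. The wording may also mean several nurses per arm, in which case the lower range applies.

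None of this touches the care route, which is a stated staffing rule and not a detail left to another document.

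**Conclusion.** The point holds for care: provider is tied to arm by the stated staffing, and neither the t-test nor the generalized estimating equations can separate the two. For scoring it holds only if the treating nurses score, and then mainly for scar formation and pain.

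The size is illustrative. Under SD 1, 20 per arm and no laser effect, type I error is about 13–23% with one nurse per arm and 7–11% with three, for a between-nurse SD of 0.2 to 0.3; a fixed half-point shift gives 34%. The documents give no estimate of the between-nurse difference, so none of these is a prediction.

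A reader might go further and say that the bias must favour the laser, or that any positive result would be worthless. The documents support neither. In the care route the better nurse could be in either arm; expectation in an unmasked scorer would more likely favour the laser, but that is not certain. The supportable conclusion is a risk of bias from unequal care, and possibly from unequal assessment, that the analysis cannot remove.

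**What to change.** 1. **Cross nurses with arm.** Have the same nurses deliver conventional care in both arms. Either the laser-trained nurse also treats control patients, or the staff nurses give conventional care in both arms and the laser-trained nurse only applies the laser.
2. **Separate scoring from treating where the roster allows.** A trained nurse who does not treat that patient and is not told the allocation scores the NOC indicators and measures length and width before treatment. The nurse who dresses the wound after the laser would not serve, since she learns the arm at the first visit. State in the protocol who scores.
3. **Record the treating nurse and the scorer at each visit** and include them in the analysis. Once nurses are crossed with arm, their effects can be estimated.

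The sample size need not change. The cost is more coordination at laser visits, up to 20 × 16 = 320 of them if every laser patient attends for the full 16 weeks. Masking stays imperfect because patients know their arm. Trial status reports that recruitment began in March 2017 and that patients are already being treated, so those treated under the old arrangement must be flagged in the analysis.

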### Randomization

During nursing consultations at the outpatient clinic, investigators will assess each patient’s eligibility for the study, according to the previously established inclusion and exclusion criteria. Once deemed eligible, the patient will be invited to participate in the study. Those who accept will be asked to sign an informed consent form.

Subsequently, an additional meeting with the research assistant, the patient will be prompted to draw a sealed brown envelope with no external notations or identification that might refer to their group allocation. Inside the envelope, there is a label indicating the group to which the patient belongs (that is, control or intervention). The envelope will then be opened by the patient himself. A research assistant putting the labels inside the envelopes before the study began. It organizes all the instruments that will be necesssary for the application of the research, confers and organizes the consultations agendas.

### Demographic and clinical variables

A structured questionnaire will be administered to all study participants to obtain sociodemographic and clinical information (age, sex, educational attainment, current medications, comorbidities, smoking, alcoholism, chronic venous insufficiency grade, ulcer duration, wound dressing regimen, nutrition, and exercise). Evaluation of the ulcer itself will be performed using the 14 NOC clinical indicators described above. Patients will be instructed to perform daily plantar flexion and extension and calf-strengthening exercises, resting in between, and taught how to dress their wounds as appropriate to their individual needs.

### Outcomes

#### Primary outcome

The primary outcome is decreased wound size and scar formation based on NOC outcome wound healing (secondary intention; 1103).Wound area in cm^2^ (measured as the product of the longest dimension in the cephalocaudal direction by the widest dimension), evaluated by a Likert scale, with 1 being the worst possible score and 5 the best possible score. Each Likert scale score of the Decreased wound size indicator has an operational definition that corresponds to the size in cm^2^.Wound covered with epithelial tissue (new pink or bright tissue that develops from the wound edges or as islands on the surface of the wound), evaluated by a Likert scale, with 1 being the worst possible score and 5 the best possible score.

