**Methods/design:**

For this prospective randomized controlled trial, 40 adult patients of both sexes with active venous ulcers will be recruited. Subjects will be selected by the sealed-envelope method without any annotation or external identification that might refer to the type of study group. At the time of unblinding, a label with the description of the group to which the patient belongs (that is, control or intervention) will be found inside the envelope. Conventional treatment (topical medication and compressive therapy) will be offered to both groups. Additionally, the intervention group will receive adjuvant low-level laser therapy. All patients will be followed weekly until ulcer healing or for a maximum of 16 weeks. Evaluation of tissue repair will be based on 14 clinical indicators drawn from NOC for wound healing (secondary intention) and tissue integrity (skin and mucous membranes). The primary endpoint will be decreased wound size and scar formation. This laser therapy is expected to enhance the quality, speed, and effectiveness of the treatment of venous ulcers, a chronic condition. This should reduce associated costs to the health service and allow patients to resume their daily activities sooner.

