### Sample size

The WINPEPI program, version 11.43, was used to calculate the sample size. A sample of 34 subjects (*n* = 17 per group) would be able to detect a 1-point difference on a NOC indicator score between group means (laser intervention versus conventional control) as significant. The indicators are scored on 5-point Likert scales (range 1 to 5), in which the lowest score represents the worst possible state and the highest score represents the most desirable state after implementation of interventions. A change in one level, i.e., one point on the Likert scale, characterizes a positive effect of the intervention implemented throughout the treatment study, according to mixed linear models and generalized estimating equations. The standard deviation common to the groups [18], with a statistical power of 80% and significance level of 5% were defined for the study. To account for possible refusals and losses to follow-up, the sample was oversized by 20%. Thus, 40 subjects (*n* = 20 per group) will be recruited.

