### Statistical analyses

Continuous variables will be expressed as mean and standard deviation or median and interquartile range according to the data distribution. Categorical variables will be expressed as absolute and relative frequencies. Generalized estimating equations will be used for comparisons between the weekly indicators, and the least-significance-difference post-hoc test will be used to assess the difference between weeks.

For quantitative variables with a normal distribution, the difference between the two groups will be compared by Student’s *t*-test. This test will also be used to analyze the means of the NOC results in relation to the decreased wound size and scar formation outcomes. The Pearson correlation coefficient will be used to evaluate the linear association between NOC results and primary outcomes. A nonparametric Mann–Whitney test will be used for comparison between the two groups regarding the characterization of ulcers.

To assess the effect size of the intervention, relative risks with 95% confidence intervals will be calculated. A two-tailed *P* < 0.05 will be considered statistically significant. All analyses will be performed in PASW Statistics, Version 18.0.

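### Two primary indicators, an unadjusted 5% level and a sample size for one indicator: the protocol does not say whether success needs one or both

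*Protocol article*

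**What the plan says.** The Primary outcome section reads: "The primary outcome is decreased wound size and scar formation based on NOC outcome wound healing (secondary intention; 1103". It then defines the two parts separately. Wound area in cm² is mapped to a 1-to-5 score, and epithelial coverage has a 1-to-5 score of its own. No sum or composite of the two is defined. The abstract repeats the pair: "The primary endpoint will be decreased wound size and scar formation".

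Statistical analyses mentions Student's t-test and adds: "This test will also be used to analyze the means of the NOC results in relation to the decreased wound size and scar formation outcomes". It plans a correlation to "evaluate the linear association between NOC results and primary outcomes", in the plural. Its only significance rule is "A two-tailed *P* < 0.05 will be considered statistically significant". It gives no split, order or success rule for the two indicators.

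Sample size says that 34 subjects, 17 per group, "would be able to detect a 1-point difference on a NOC indicator score between group means", in the singular, "with a statistical power of 80% and significance level of 5% were defined for the study". The SD is cited from a reference and its value is not given. Recruitment is raised to 40, 20 per group, for refusals and losses.

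**The concern.** One indicator at 5% and 80% power describes neither of the two plain ways to read a pair of primary indicators, each tested at 5%. If success on either is enough, there are two chances of a false positive. If success on both is needed, there are two chances to miss a real effect.

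The practical risk is a split result. If wound size reaches significance and scar formation does not, or the reverse, this document cannot say whether the trial met its primary objective. That would then be decided with the results in view.

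**Working it through.** **Inputs**
- From Sample size: 17 evaluable per group (20 recruited), a difference of 1 point, 5% level, 80% power. From Statistical analyses: two-tailed testing.
- Not in the document, so assumed: the SD, the correlation ρ between the two indicators (shown from 0 to 0.9), the same SD and a 1-point effect on both, and approximately normal scores compared once by t-test.

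**Step 1. The plan's own figure.** Without an SD it cannot be reproduced from the stated inputs alone. With an assumed SD of 1.0 and one indicator, the normal formula is n = 2·SD²·(1.96 + 0.84)²/1² = 15.7, so 16 per group. The exact t-test needs 16.7, so 17 per group, with power 80.7%. The stated 17 therefore fits **one** indicator at two-sided 5% with an SD near 1.0. Solving the t-test for exactly 80% power at 17 per group gives SD = 1.009, which is used below. The inflation is 34 × 1.2 = 40.8, against 40 planned.

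**Step 2. Independent indicators (ρ = 0), by hand.**
- Either at 5%: error = 1 − 0.95² = 9.75%.
- Both at 5%: joint power = 0.80² = 64%.
- Both at 5%, 20 per group: single-indicator power is 86.3%, so joint power = 0.863² = 74.5%.
- Either at 2.5% each: error = 1 − 0.975² = 4.9%. Power per indicator is 70.3%, so the chance of at least one success = 1 − (1 − 0.703)² = 91%.

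**Step 3. Correlated indicators.** I simulated two t-tests on bivariate normal scores with SD 1.009, 400,000 trials per setting:

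| ρ | Either at 5%: error | Both at 5%: power, 17 per group | Both at 5%: power, 20 per group | Either at 2.5%: error | Either at 2.5%: chance of at least one success, 17 per group |
|---|---|---|---|---|---|
| 0 | 9.8% | 64% | 75% | 4.9% | 91% |
| 0.5 | 9.1% | 69% | 77% | 4.7% | 85% |
| 0.8 | 7.9% | 73% | 81% | 4.1% | 79% |
| 0.9 | 7.1% | 75% | 82% | 3.6% | 77% |

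Under a fixed sequence (first indicator at 5%, second at 5% only if the first succeeds), family-wise error is at most 5% and power for the first indicator is 80%. The chance of claiming the second equals the chance that both reject, which is the 17-per-group column for both: 64% to 75%.

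**The case against.** **The rule may sit in an analysis plan that is not shown.** A journal article condenses, and multiplicity is often settled elsewhere. An absent rule alone would be no finding. But this article itself fixes two primary indicators, a single unadjusted 5% level and a power statement for one indicator, and these do not fit together. A rule set elsewhere would still have to be reconciled with the stated 80%.

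**The wording reads as a conjunction.** The outcome is named in the singular and joined by *and*, under one NOC outcome. On that reading error is not inflated, and only the loss of joint power remains. This is fair: the 7% to 10% error applies only to an either-rule that the document never states. Against it, the analysis section speaks of primary outcomes in the plural.

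**Forty will be recruited.** If all 20 per group were evaluable, joint power would be 75% to 82%, reaching 80% at a correlation of about 0.8. But the stated 80% rests on 17 per group, and the extra patients are there to cover losses.

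**Two stronger readings are tempting and not supported.** First, a reader might infer that the design must break either its 5% or its 80%. It need not. Allowing either indicator at 2.5% keeps error below 5%, with a 77% to 91% chance of at least one success at 17 per group. The fault is that no such rule is stated. Second, a reader might infer that each primary indicator is also tested between groups every week by generalized estimating equations, which would add further chances of success. The text assigns that model to comparisons of the weekly indicators and the post-hoc test to differences between weeks. It does not clearly name either as a primary between-group test, so I put no figure on this.

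**Conclusion.** The point holds as a mismatch between endpoint, significance level and sample size. At 5% for each indicator, an either-rule gives a family-wise error of about 10% to 7%. A both-rule controls error but gives joint power of about 64% to 75%, or 75% to 82% with no losses. These sizes rest on the back-solved SD of about 1.01, equal 1-point effects and correlations of 0 to 0.9, none of which the document gives. The direction does not depend on the exact values: for any correlation below 1, two unadjusted 5% tests do not keep both the 5% error and the 80% power planned for one. It is not a claim that the trial is too small, since a stated rule repairs it at the present size.

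**What to change.** State one rule, in the protocol and any analysis plan, before anyone compares outcomes by group:

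- **(a) Fixed sequence.** Test decreased wound size at two-sided 5%, then scar formation at 5% only if the first is significant. The one-indicator calculation then applies to the first test, provided the cited SD is suitable for that indicator. Disclose that power to claim scar formation is also about 64% to 75%.
- **(b) Both required.** Keep 5% for each and restate joint power as about 64% to 75%.
- **(c) Either, at 2.5% each.** Error stays at or below 5%. State about 70% power per indicator and a 77% to 91% chance of at least one success.

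Under any rule, print the SD used. Name one between-group test and one time point for the primary analysis, and label other weeks and methods supportive. According to the Study protocol section, monitoring stops at complete repair, so say how patients who heal earlier are scored at that time point, for example by carrying forward the healed score.

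Cost: no extra patients. The trial accepts a less favourable stated power or a conditional claim on the second indicator. Enrolment is under way and patients open their own allocation envelopes, so this should be a dated, documented amendment that records that outcomes had not been compared by group.

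### The named t-test on the primary NOC scores takes no account of the baseline score, although the wound-size score appears to reflect ulcer size at entry; precision is lost, not validity

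*Protocol article*

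**What the plan says.** The Primary outcome section names two NOC indicators: "The primary outcome is decreased wound size and scar formation based on NOC outcome wound healing". Area is "measured as the product of the longest dimension in the cephalocaudal direction by the widest dimension" and is then scored from 1 (worst) to 5 (best). On the anchoring of that score the section says "Each Likert scale score of the Decreased wound size indicator has an operational definition that corresponds to the size" in cm². It mentions neither size at entry nor percent change, and it does not print the limits of the levels.

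The Statistical analyses section introduces Student's t-test for comparing the two groups and adds: "This test will also be used to analyze the means of the NOC results in relation to the decreased wound size and scar formation outcomes". That section also says "Generalized estimating equations will be used for comparisons between the weekly indicators", with a least-significant-difference post-hoc test between weeks. The Sample size section also refers to mixed linear models and GEE, but the quantity it powers is a 1-point difference between group means. No baseline covariate is named in any of these places.

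At entry, the only exclusion made for the extent of the ulcer is the circumferential one. The Randomization section describes drawing sealed envelopes and mentions no stratification by size. Under Demographic and clinical variables, "Evaluation of the ulcer itself will be performed using the 14 NOC clinical indicators described above", so a baseline NOC score should exist for each patient.

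**The concern.** If each level stands for a range of current area, the indicator records how large the ulcer is at the visit and not how much it has shrunk. Two patients with the same proportional healing can then finish at different scores because they started at different sizes. That variation between patients has nothing to do with treatment.

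A t-test on follow-up means leaves this variation in the error term. With 17 to 20 per arm, two things are at stake. Power is lower than the same patients could give. In addition, an arm that happens to draw smaller ulcers starts ahead, and nothing in the named comparison corrects for it. As described, eligibility, allocation and the named test all leave entry size unhandled.

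**Working it through.** **Inputs.** From Sample size: difference 1 point, power 80%, 5% significance level, 17 per group, 20 per group after oversizing. From Statistical analyses: two-tailed test. Not given: the SD (attributed to a reference) and the correlation r between baseline and follow-up score. Both are assumptions below.

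**1. The plan's own figure.** The normal approximation is n per arm = 2 × [SD × (1.960 + 0.842)]² / 1².
- SD 1.00: 15.7, rounded up to 16.
- SD 1.02: 16.3, rounded up to 17.
- SD 1.04: 16.98, rounded up to 17.

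The formula therefore returns 17 for an SD between about 1.01 and 1.04. With the exact two-sample t-test, SD 1.00 needs 16.7 (rounded up to 17), and SD 1.009 gives 80.0% power at 17 per arm. The stated 17 is consistent with an SD of about 1.0. I use 1.009, so that unadjusted power starts at 80%.

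**2. Power with baseline adjustment, 17 per arm.** Residual SD = 1.009 × √(1 − r²). Noncentrality = 1 / [residual SD × √(2/17)]. The t distribution has 32 degrees of freedom unadjusted and 31 adjusted.

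| r (assumed) | 1 − r² | Residual SD | Noncentrality | Power |
|---|---|---|---|---|
| 0 (t-test) | 1.00 | 1.009 | 2.89 | 80.0% |
| 0.3 | 0.91 | 0.963 | 3.03 | 83.5% |
| 0.5 | 0.75 | 0.874 | 3.34 | 89.8% |
| 0.7 | 0.51 | 0.721 | 4.05 | 97.5% |

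Starting instead from SD 1.02 with the normal approximation gives 81.5%, 85.0%, 91.0% and 97.9%. The result does not hinge on the exact SD or formula.

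**3. Chance imbalance at entry.** The difference between arms in mean baseline, in SD units, has standard error √(2/n). The probability that it exceeds 0.5 SD in either direction is 2 × [1 − Φ(0.5 / √(2/n))].
- n = 17: 0.5 / 0.343 = 1.46, probability 14.5%.
- n = 20: 0.5 / 0.316 = 1.58, probability 11.4%.

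Given an imbalance of 0.5 SD, the unadjusted difference shifts on average by r × 0.5 × SD of the score. With an SD of about 1.0, that is about 0.15, 0.25 or 0.35 points for r = 0.3, 0.5 or 0.7, against a target of 1 point.

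**4. Validity.** Randomization balances entry size on average, and the standard error of the t-test already allows for chance imbalance. A simulation under no treatment effect agrees. It used 17 per arm, 2,000 runs per setting, an assumed median entry area of 8 cm², log-SD 0.8 or 1.2, and three assumed sets of bands. The t-test on the banded score rejected in 4.2% to 5.5% of runs.

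**The case against.** The strongest reply is that nothing here is an error. The t-test holds its level, chance imbalance is part of its standard error, and GEE on the weekly scores may well include the first assessment. How baseline enters a model is often left to an analysis plan, and none is shown. Much of this stands. A reader might infer that the primary test is biased or that baseline goes wholly unused, and the document supports neither. What remains is that the article does name a test for the two primary indicators, that this test has no baseline term, and that the post-hoc comparison described for the GEE is between weeks and not between groups.

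Three other stronger readings are tempting.

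- **Ceiling and band effects.** One could say that small ulcers start near the top of the scale, or that large ones can shrink greatly within one level. With invented cut-points at 1, 5, 10 and 20 cm², an ulcer going from 60 to 24 cm² keeps its score while one going from 6 to 4.5 cm² gains a level. But the real cut-points and the size distribution are not printed, so this is a possibility and not a finding. For the same reason I quote no simulated power: such figures would reflect the chosen bands.
- **Co-interventions.** The section on confounding variables says "The impact of each management strategy on the outcomes will be controlled by monitoring the following confounding variables" and lists pharmacotherapy and co-intervention elsewhere. One might infer adjustment for events after randomization, with resulting bias. The Statistical analyses section plans no such adjustment, and monitoring may mean only recording.
- **Area thrown away.** No analysis of area as a continuous measure is named. The article also does not say whether the cm² value is stored once the score is assigned, so one cannot assume that it is available.

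**Conclusion.** The point holds as one of efficiency and robustness. The comparison named for the primary indicators ignores a baseline value that the trial collects and that probably predicts the outcome. At 17 per arm, adjustment would lift power from about 80% to between about 84% and 97%, with about 90% at a correlation of 0.5. It would also remove dependence on an entry imbalance that exceeds half an SD in about one trial in seven (17 per arm) to one in nine (20 per arm).

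This rests on three assumptions: the SD of about 1.0, which is back-solved; the correlations, which are not known for this scale; and the plain reading that the score levels are ranges of current area. The gain may differ between the two indicators. If scar formation varies little among open ulcers at entry, its baseline score will explain little and the benefit there will be small. The planned sample size is not in dispute.

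**What to change.** - Replace the t-test on each primary indicator by ANCOVA with that indicator's baseline NOC score as covariate. Alternatively, take the group contrast from the planned GEE with the same covariate, and state that contrast. For wound size, baseline area may be used in place of the baseline score. Entering both adds little, because the score is derived from the area.
- As a supportive analysis, where the measured cm² is recorded, compare area between groups adjusted for baseline area. Use a scale that allows zero, because healed ulcers have area 0 and a plain logarithm is undefined there. Percent change, or log(area + a constant fixed in advance), would serve.
- Confirm that the cm² value is kept at each visit as well as the score.

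The cost is about one degree of freedom per model and a change of analysis wording. The adjusted score analysis needs no new measurement. The supportive analysis depends on the area having been stored. The article reports enrollment as ongoing, and the change should be fixed before outcomes are compared by group.
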